## Abstract

**Background:**

Obsessive-compulsive disorder (OCD) in children can lead to a huge burden on the concerned patients and their family members. While successful state-of-the art cognitive behavioral interventions exist, there is still a lack of available experts for treatment at home, where most symptoms manifest. Internet-based cognitive behavioral therapy (iCBT) could overcome these restrictions; however, studies about iCBT in children with OCD are rare and mostly target computerized self-help resources and only email contact with the therapist. Therefore, we intended to build up and to evaluate an iCBT approach for children with OCD, replacing successful elements of traditional in-office face-to-face CBT, with face-to-face teleconferences, online materials, and apps.

**Methods:**

With the help of a pilot feasibility study, we developed the iCBT consisting of 14 teleconference sessions with the child and parents. The sessions are supported by an app assessing daily and weekly symptoms and treatment course completed by children and parents. Additionally, we obtain heart rate and activity scores from the child via wristbands during several days and exposure sessions. Using a waiting list randomized control trial design, we aim to treat and analyze 20 children with OCD immediately after a diagnostic session whereas the control group of another set of 20 OCD patients will be treated after waiting period of 16 weeks. We will recruit 30 patients in each group to take account for potential dropouts. Outcomes for the treatment group are evaluated before randomization (baseline, t0), 16 weeks (end of treatment, t1), 32 weeks (follow-up 1, t2), and 48 weeks after randomization (follow-up 2, t3). For the waiting list group, outcomes are measured before the first randomization (baseline), at 16 weeks (waiting list period), 32 weeks (end of treatment), 48 weeks after the first randomization (follow-up I), and 64 weeks after the first randomization (follow-up II).

**Discussion:**

Based on our experience of feasibility during the pilot study, we were able to develop the iCBT approach and the current study will investigate treatment effectiveness. Building up an iCBT approach, resembling traditional in-office face-to-face therapy, may ensure the achievement of well-known therapy effect factors, the acceptance in both patients and clinicians, and the wide distribution within the health system.

**Trial registration:**

ClinicalTrials.govNCT05037344. Registered May 2019, last release August 13th, 2021.

## Background

The mental health of children and adolescents is a high-priority area and there is a need for effective and easily accessible treatments. Obsessive-compulsive disorder (OCD) is characterized by fear, worry-provoking intrusive thoughts, and repetitive behaviors that reduce the associated distress. Without treatment, OCD is a chronic and highly impairing disorder, with a population prevalence rate between 1 and 3% [1].

Cognitive behavioral therapy (CBT) is a highly effective treatment for OCD in children and adults [2, 3]. During exposures with response prevention (ERP), patients are confronted with their intrusive thoughts and preceding situations; patients learn to stop their repetitive behaviors followed by a natural decline in distress and learning experience that intrusive thoughts are harmless. Unfortunately, there is limited availability of therapists adequately trained in this specific CBT procedure for OCD. In addition, ERP is hardly used during CBT because of practicability in everyday therapeutic life, or negative assumptions of the therapists, just to mention a few [4]. Apart from this, one major obstacle is also the fact that access to appropriate treatment is particularly difficult for children and adolescents in rural areas due to fewer psychotherapists being locally available [5. Accordingly, too few children with OCD get appropriate help [6]. Medication is much more accessible than CBT [7]. Another problem within face-to-face settings is that the psychotherapist often acts as security signal preventing a strong realistic symptom provocation. In addition, symptoms are especially present at home and, therefore, therapy should be more efficient, when these symptoms are treated in the corresponding triggering environment. OCD patients themselves also sometimes refuse psychotherapy due to avoiding behavior, fear of stigmatization, geographical distance to experts and time restrictions, especially in rural areas [8]. Patients, therefore, often suffer from a long delay until getting effective treatment. Late treatment onset is critical as the longer a patient is without effective treatment, the more likely their symptoms are to become chronic [9]. Accordingly, internet-based treatments with CBT experts could address an important gap in availability of treatments [10]. Moreover, due to the Covid-19 pandemic, psychotherapy was only possible via teleconferences which pushed acceptance of psychotherapists and patients forward for this new method more than ever before. iCBT could be especially attractive for pediatric patients as 90–96% of young people aged 12–24 have good internet accessibility and their ability to use new media platforms should be high [11]. It can be also cost-effective [12]. Furthermore, it may even be possible to reach and treat more patients across the country. The inclusion of parents in the therapeutic process is also more practical and easier via internet, as compared to traditional face-to-face approaches, as they can be part of the process no matter their location, as long as they have an internet connection.

Studies on iCBT approaches are encouraging, especially regarding anxiety disorders or depression. The findings of studies, reviews, and meta-analyses in patients (mostly adults, but also in children) suggest that CBT programs with computerized elements (e.g., online material, email contacts) are just as effective as CBT from traditional face-to-face therapies [13–20]. There are also a few studies reporting promising results on patients with OCD [21]. Studies using self-help iCBT in adults or children with OCD revealed therapy success [22–25]. Other studies in adults and children with OCD used therapist-assisted text-message-based iCBT approaches which were found to be very effective, although therapists in some of these studies were not clinical experts [11, 26–30]. There are also results revealing long-term efficiency and cost-effectiveness [16, 31]. Concurrently, one study compared therapist-guided iCBT, unguided iCBT, and traditional face-to-face therapy in adults with OCD to get more information about the requirement of therapist involvement, which may be an important factor for a successful therapeutic intervention [32]. Reviews dealing with self-help interventions in OCD suggest that the more a therapist is involved in interventions, the more likely it is that there are successful treatment outcomes [33, 34]. There have only been a few iCBT approaches using telephone conferences between patients and therapists for OCD, and the results are promising. However, due to small samples sizes, treatment by less trained therapists, or often a lack of control groups in these studies [5, 35–37], further research is needed; hence, the present study aims to address some of these caveats.

Although iCBT approaches exist, it is evident that more studies on specific disorders and more studies in children and their families are needed. Therapist contact seems to be an important moderator and may be especially important for long-term benefits and patient adherence [15]. Nevertheless, most existing iCBT programs either use self-help elements, lack a control condition, lack visual contact with the therapist, or provide therapy only by trained practitioners rather than psychotherapy experts. An approach replacing traditional face-to-face CBT with online elements, such as teleconferences, whilst following similar protocols to traditional settings, would increase acceptability and the distribution of these tools in the health system. Finally, and most importantly, such an approach would contribute to secure and improve the health of the patients. Enriching such an approach with further benefits of new media, such as an app-based assessment of daily symptoms, avoidance behavior, daily hassles, and functioning or therapeutic homework by apps may additionally increase the health benefit over traditional face-to-face psychotherapies as well as the self-efficacy of the patients.

Therefore, we continuously met with international experts on OCD treatment to develop evidence-based ideas for an internet-teleconference-based psychotherapy manual and a supporting app. Together, with the IT department of the university hospital and an external programmer, we developed a data security concept and IT software to use these technologies and to transfer the data safely into internal databases. We already treated OCD patients with this approach in a pilot study and could show that patients appreciated our intervention. Therefore, we now want to go beyond feasibility and test the effectiveness of our treatment in a waiting list design. We hypothesize that symptoms decline over treatment in comparison to the waiting group that later will also benefit from the treatment. The long-term goal is to develop an effective and acceptable internet-delivered pediatric OCD treatment intervention which can also be generalized for the treatment of other disorders.

## Methods/design

### Subjects

The study has a parallel group design with an experimental group receiving treatment after baseline assessment and a waiting group receiving treatment after a waiting period of 16 weeks, comparably to the length of treatment. The planned allocation ratio is one expecting superiority in symptom reduction in the experimental group. Patients are recruited by licensed child and adolescent psychotherapists who work at the university hospital of Tübingen. A Google AdWords advertising and recruitment campaign is carried out in cooperation with the Department of Communication at the University Hospital Tübingen.

To deal with probable dropouts, we planned to enroll 30 children with OCD in the experimental group and 30 children with OCD in the waiting group with the aim to finally analyze 20 patients in each group. Including clinical considerations, this was a realistic sample size, we were able to achieve in a 3-year period. Sample size was planned according to the following considerations. As primary outcome, we considered the CY-Bocs score. Our primary assessment endpoint was the comparison at t1 post-treatment between the treatment and the waiting group. In the pilot study of our treatment protocol using a pre/post-assessment with *N* = 9 children with OCD [38], effect size was *d* = 2.02. Therefore, we knew, that our treatment protocol most likely will lead to symptom reduction. Effect size of another study comparing webcam-delivered CBT in 16 children with OCD with a waiting group of 15 children with an ANCOVA on post-treatment CY-Bocs scores, covarying baseline CY-BOCS scores, showed a significant effect of treatment with *η*^2^ = 0.36 [37]. A further study in adults with OCD [39], comparing face-to face exposure treatment (*n* = 20) with a waiting group (*n* = 16), revealed an effect size of *d* = 1.001 for the CY-Bocs comparison at post-treatment. Therefore, we estimated that the effect in our study as a comparison of CY-Bocs scores of an effective treatment in comparison to the waiting group at t1 will be high. We expected that there will be a significant difference comparing 20 patients with treatment with 20 patients in the waiting group at t1.

All participants and their parents provide informed consent. On the consent form, participants are asked to allow the use of their data also for future projects of the department and the study team. The consent forms are available from the corresponding author on request. The trial does not involve collecting biological specimens for storage. Patients will be recruited through established OCD outpatient units in Tübingen and Cologne (Germany), OCD Society, the Clinic’s homepage, schools, Google AdWords, an interview with an influencer suffering from OCD, and local psychiatrists and psychologists in Tübingen.

After a telephone interview and a first visit at our research department in Tübingen to verify the suitability for taking part in the study, and the face-to-face diagnostic session, participants will be randomized to the experimental or waiting list groups. Inclusion criteria will be children and adolescents (aged between 6 and 18) with a primary diagnosis obsessive-compulsive disorder according to DSM-5, a CY-BOCS score higher than 16 and at least one primary caretaker, German-speaking (child & caretakers), and a family home equipped with a broadband internet connection. Psychiatric comorbidities are allowed as long as the comorbid disorder does not have a higher treatment priority than OCD. Participants are excluded if they have an IQ below 70, do not speak or understand German, have a psychiatric comorbidity or suicidality that makes participation clinically inappropriate, or if they should be treated in the hospital. Medication is allowed if treatment was stable for 6 weeks before inclusion into the study and will then be taken during the trial. Furthermore, patients will be excluded in case of drug addiction or if the family seems to be severely psychologically burdened such that participation in the sessions and support of the children during the trial will not be possible. This will also be discussed in the steering board of our study team. While participating in the study, no other psychological treatment is allowed. If reporting side effects, or if wished by the patients, the patients will be excluded from the study and transferred to another more appropriate therapy option.

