The documentation of the follow-ups including questionnaires will be recorded manually in the respective patient folders and kept locked in the cabinets in the clinic. If participants do not at all adhere to the protocol, are not motivated, or want to quit the study, they will drop out of the study; however, this will be the last option and motivational work will be done in advance. All planned outcomes will, nevertheless, be assessed for dropouts. A digital list of dropouts is kept within the study team and we note the reason for their dropout. Information about non-compliance, problems, or harms are continuously documented during the trial after every treatment session.

Data collection is monitored by our study team who meets every week. If problems with data collection become obvious, the team decides together about required next steps to ensure data quality, e.g., telephone call with the participants to encourage data completion. There is no external supervision of the data. As we use a low-risk intervention, there will be no trial auditing. As mentioned, the project team meets every week to discuss trial conduct.

There are no planned interim analyses that might lead to trial finalization. Trial would be stopped only if the team observes severe clinical reasons to stop the trail. These are, however, not expected because of our preliminary study and the fact that treatment is based on state-of-the art therapy methods. Data are in part only evaluated when needed, for example to show first preliminary results in presentations on conventions. If there are any changes to the protocol, these are discussed within the study team and the sponsor and changes are documented. If the protocol must be changed, the trials registry ClinicalTrials.gov will be updated. Only the study team has access to the final dataset.

Results will be disseminated in scientific papers, presentations in conventions, or within the university hospital or public media. Additionally, the funder will be informed about the results.

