### Statistical analysis

We will use SPSS for data analysis. For all diagnostic parameters, we will assess treatment efficiency with ANOVAs with group as the between-subject factor (treatment group (experimental group), waiting group (control group)) and time (t0 = diagnostic assessment, t1 = end of treatment treatment group/end of waiting period, t2 follow-up I treatment group/ end of treatment waiting group, t3 follow-up II treatment group/follow-up I waiting group, t4 follow-up II waiting group) as the within-subject factors. The most important outcome analysis will be the comparison in CY-Bocs score between the treatment and waiting group at t1. A comparable repeated measures ANOVA will be conducted for the time between t0 and t1 concerning weekly app questions/aggregated physiological data over the week but the time factor is week 1 to week 14. This is to indicate weekly symptom course and differences to the data assessed during waiting in the waiting group. Deeper analyses will concentrate on symptom course and intra-individual variability for daily app questions. Answers of child, parents, and therapist are correlated to investigate their agreement. Additionally, we will evaluate if avoidance behavior during exposures is related to treatment success within exposures with correlations of severity of avoidance behavior and anxiety decrease during exposures. We will also evaluate the influence of avoidance behavior during exposures and during the day on symptom decrease over the treatment assessed via CYBOCs with correlations. Descriptively, we evaluate the answers of our post-experimental questionnaire to treatment compliance, feasibility, and satisfaction as well as the within session questions. We will also compare the number of dropouts between the experimental group and the waiting group with *t*-tests. Integrity is descriptively evaluated with the session questionnaires provided by the therapist. Data will be analyzed to see if missing values are correlated with any basic effects. Little’s Missing Completely at Random Test (MCAR) will be used to check whether they are randomly distributed. The recommendations of the National Research Council will be followed. If there are missing data, we will report analyses with all data available. There will be enough data for the comparison between t0 and t1. A second set of analyses will also include the follow-up assessments where some missing data might appear. We might additionally report analyses with imputations. Significance will be followed up with Bonferroni-corrected paired contrasts. Alpha level is 5% and all tests will be conducted two-tailed.

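### The protocol does not secure a t1 comparison of all randomised children as allocated: its statements on exclusion, dropouts and analysed numbers are unreconciled, and the named ANOVA uses only observed t1 scores

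*Protocol article*

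**What the plan says.** All references are to the protocol article.

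- **Subjects, planned numbers.** "To deal with probable dropouts, we planned to enroll 30 children with OCD in the experimental group", and the same number in the waiting group, "with the aim to finally analyze 20 patients in each group". The abstract repeats the allowance: "We will recruit 30 patients in each group to take account for potential dropouts". No dropout rate is given.
- **Subjects, leaving the study.** "If reporting side effects, or if wished by the patients, the patients will be excluded from the study"; they are then moved to another therapy. The sentence follows the ban on other psychological treatment during participation, so it operates after randomisation.
- **Study procedure and design.** Children who do not adhere, lack motivation or want to stop drop out as a last resort. But: "All planned outcomes will, nevertheless, be assessed for dropouts".
- **Study procedure and design, randomisation list.** Eight blocks of six, three per group in each block.
- **Statistical analysis.** An ANOVA with group and time as factors, the main comparison being CY-BOCS at t1. With missing data, analyses of all available data will be reported, and National Research Council recommendations will be followed. "There will be enough data for the comparison between t0 and t1". A second set of analyses adds the follow-ups. "We might additionally report analyses with imputations".

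**The concern.** The t1 difference is a randomised comparison only if the children in it are those who were randomised, in their allocated groups. The Subjects section gives grounds for removal that are plausibly related to treatment and outcome. Side effects of the internet therapy can arise by t1 only in the treated group, because the waiting group has not started. Wishing to leave may mean burden or non-response in one group and impatience in the other.

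Whether such children stay in the primary comparison depends on which sentence is followed. If they leave the study entirely, they have no t1 score, and an ANOVA on observed scores omits them. If dropouts are assessed as promised and all available data are used, most of them are kept. The protocol does not say which prevails, and the primary efficacy result rests on it.

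**Working it through.** **1. Implied loss.** The article gives no rate, so it has to be backed out.

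- From the enrolment target: 1 − 20/30 = 33.3% per group. Reversed, 20/(1 − 1/3) = 30. This is circular and does not check the plan's figure independently.
- From the randomisation list: 8 × 6 = 48 slots, 24 per group, so 1 − 20/24 = 16.7%.

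The two sections therefore imply different losses, and both are carried forward.

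**2. Where a child without t1 goes.** The primary contrast is at t1. An ANOVA on t0 and t1, or a simple comparison at t1, needs an observed t1 score, so a child without one contributes nothing to the contrast. Follow-up gaps need not matter here, because the article puts the follow-ups in a second set of analyses.

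**3. Bias if the loss is not random (assumptions, not in the article).** Let a share L of the treated group be lost, and let those children score D SD worse at t1 than those retained. Waiting-group loss is taken as random. The retained treated mean is then better than the full-group mean by L × D:

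| D (SD) | L = 33.3% | L = 16.7% |
|---|---|---|
| 0.25 | 0.08 | 0.04 |
| 0.50 | 0.17 | 0.08 |
| 0.75 | 0.25 | 0.13 |
| 1.00 | 0.33 | 0.17 |

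If instead the waiting group loses its worse cases, the sign reverses. If loss is random in both groups, the bias is zero.

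**4. False-positive rate at 20 per group.** Two-sided 5% t-test, no true effect, mean shift L × D, SD 1, noncentral t:

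- L = 33.3%: 0.058 at D = 0.25, up to 0.177 at D = 1.0.
- L = 16.7%: 0.052 at D = 0.25, up to 0.081 at D = 1.0.

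A simulation (20,000 runs per case) dropped 10 of 30 treated children with a dropout–outcome correlation of 0, 0.2, 0.4 or 0.6. It gave error rates of 0.050, 0.065, 0.102 and 0.181.

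**5. Effect on power of keeping everyone.** The article states neither power nor a design effect. The effect detectable with 80% power (t-test, SD 1) is 0.91 SD at 20 per group, 0.83 at 24 and 0.74 at 30. At the cited adult effect, d = 1.001, power is 0.87 with 20 per group and 0.97 with 30. If the lost third of the treated group gained nothing (an extreme assumption), the effect over all 30 would be 1.001 × 2/3 = 0.67 SD, with power 0.72. With 24 per group and one sixth gaining nothing, it would be 1.001 × 5/6 = 0.83 SD, with power 0.81.

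**The case against.** The strongest reply is that no completer analysis is declared. Twenty per group can be read as a sample-size target after a dropout allowance, not as a definition of who is analysed. No sentence says that dropouts' t1 scores are discarded. The article promises outcome assessment for dropouts, analyses with all available data, and adherence to National Research Council recommendations. **All of this stands.** A reader might infer that the plan deliberately builds in a completer analysis and has given up the protection of randomisation. The text does not support that.

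Three further inferences also fail:

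- **That the statement about enough t0–t1 data contradicts the dropout allowance.** The plan treats 20 per group as sufficient and recruits above it, so the two are compatible.
- **That Little's test is used to justify complete-case analysis.** It is described only as a check of whether missing values are randomly distributed; no analysis choice depends on it.
- **That the effect will be overstated by half.** Comparing a 1.0 SD completer effect with 0.67 SD over all randomised children needs a full third lost, zero benefit in all of them and no t1 data, against the article's own promise. The two figures are also partly different target quantities.

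It can also be said that missing-data detail belongs in an analysis plan that is not shown. That holds for fine detail. It does not cover the exclusion rule, the analysed number, the ANOVA and the optional imputation, which the article itself fixes and does not reconcile. Nor does a promise to use all available data help a child whose t1 was never obtained.

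**Conclusion.** The point holds as an unsecured primary comparison. The passages on analysing 20 of 30 and on exclusion after randomisation point one way; those on assessing dropouts and using all available data point the other. No sentence ties the t1 contrast to all randomised children as allocated. Applied literally, the exclusion rule and the ANOVA can omit children for treatment-related reasons.

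Bias of 0.08–0.33 SD (33% loss) or 0.04–0.17 SD (16.7% loss) favouring treatment is a conditional range. It requires that lost treated children do 0.25–1.0 SD worse, that waiting-group loss is random, and that none of the lost children supply t1. Actual size and direction cannot be known from the article. Against the cited effects (d = 1.001 in adults; η² = 0.36 in children, d about 1.5), such a bias would more likely distort the estimate than create the whole finding.

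**What to change.** Reconcile the Subjects, Study procedure and design, and Statistical analysis sections with these statements:

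1. Every randomised child is analysed in the allocated group.
2. Leaving treatment or the waiting period, for whatever reason, does not end the t1 CY-BOCS assessment, subject to consent. The article already promises this for dropouts; it should expressly cover children excluded under the Subjects section.
3. The primary t1 analysis is a likelihood-based mixed model using t0 and t1, or multiple imputation, in place of the ANOVA on observed cases.
4. One sensitivity analysis allows data to be missing not at random, for example reference-based imputation for treated dropouts. Completers are shown only as supportive.

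Item 2 matters most: a mixed model or standard imputation assumes that missingness is explained by observed data and cannot fully replace scores never collected. The Trial status section says that recruitment closed in December 2020 and data preprocessing was to start in December 2021, so t1, at 16 weeks, would mostly have passed. Item 2 then also means reporting, by group, how many randomised children left, why, and how many have t1.

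The cost is revised wording, slightly more analysis work and some effort to obtain t1 from children who leave. The estimate may be smaller than one from completers.
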